**Conclusions:**

Few suicide risk models derived from administrative and clinical data have been tested in real world care settings. This trial will determine whether the use of such a risk model reduces suicide attempts compared to usual care. By describing important implementation factors, use of such risk models, if effective, may be accelerated for other health care systems.

**Trial registration:**

ClinicalTrials.gov NCT06060535.

**Supplementary Information:**

The online version contains supplementary material available at 10.1186/s12888-025-06760-0.

## Background

Despite local, state, and national prevention initiatives, age-adjusted suicide rates in the US increased by 37% from 1999 to 2018, then declined 5% from 2018 to 2020 but returned to near peak levels in 2021 and 2022 [1, 2]. Suicide remains one of the top ten leading causes of death among individuals aged 10–64 years old [3]. In 2022, more than 49,000 individuals in the U.S. died by suicide and 1.6 million adults attempted suicide [2]. Concern about rising suicide rates prompted the National Action Alliance for Suicide Prevention and the US Surgeon General to publish the 2024 *National Strategy for Suicide Prevention (NSSP)* [4]. According to the NSSP report, one of the most promising environments to implement suicide prevention practices is health care, where clinicians can be trained to detect suicide risk and intervene with effective care [5]. This is important given that, in one large study across eight health systems, > 83% of individuals who die by suicide and > 92% of those who attempt suicide had a health care visit within 12 months of the suicide event [6–8].

Over the last two decades numerous prevention approaches have been developed and implemented in health care settings, including a national movement to adopt strategies consistent with the Zero Suicide (ZS) framework [10–13]. While these tools have demonstrated ability to identify some individuals at risk, there are many barriers that may prevent identification of others. To fill these gaps and overcome barriers, the Mental Health Research Network (MHRN) [14] developed suicide risk identification models derived from electronic health records (EHR) and insurance claims data. Previous suicide risk models used samples consisting of military or veteran populations that were predominantly male [15, 16]. In contrast, the MHRN suicide risk identification models include data from approximately 20 million visits made by three million patients at seven large integrated health care systems, with broad diversity in sex, age, race, ethnicity, income, education and insurance [17]. The resulting models outperformed risk stratification based solely on the PHQ9 suicide ideation/self-harm question (item 9) and most other published EHR data-based models [16, 18, 19, 20–26] with C-statistics for the MHRN models ranging from 0.83 to 0.86 [17].

The MHRN risk model development and validation studies demonstrated accuracy but did not evaluate whether the models increase identification (screening) and recognition (risk assessment) or result in patients receiving more suicide prevention services (treatment) and fewer crisis services or making fewer suicide attempts. The current study is designed to answer these important implementation questions and to understand factors that could support rapid scale-up and widespread use should the risk model prove effective. This study combines the MHRN suicide risk identification model (to flag patients estimated to be at risk for suicide) and the ZS framework (to identify, engage, and treat patients identified at risk for suicide) in an innovative approach across three integrated health care systems’ behavioral health clinics to increase the reach and effectiveness of suicide prevention care models.

## Methods

### Objectives and hypotheses

The current study will test the implementation of the MHRN suicide risk model in behavioral health clinics to facilitate identification, recognition, and engagement in supportive suicide prevention services among individuals estimated to be at risk for suicide. The study’s main aim is to examine the effectiveness of a suicide risk model on fatal and non-fatal suicide attempts (primary outcome). The secondary outcome analyses examine the following questions: Are patients who receive care in the behavioral health intervention clinics more likely to be referred to and receive supportive outpatient behavioral health services than patients in usual care clinics? Are they more likely to receive supportive services sooner after risk recognition than they would have before the risk models were used, or earlier than patients in usual care clinics? Are they less likely to require crisis services and less likely to attempt suicide? Specifically, we will test the hypothesis that the risk model will lead to a reduction in suicide attempts (primary outcome) and an increase in referrals to, and receipt of, supportive outpatient services (secondary outcome).

In secondary analyses, we will determine whether implementing a suicide risk model into a suicide prevention care model improves identification of patients at risk for suicide attempt (suicide screening practices); that is, whether the enhanced identification using a risk model improves upon self-reported risk screening relied upon in usual care. Specifically, does the risk model (intervention) identify additional patients for screening who would not be identified in the course of usual care? How many additional patients are recognized (complete a risk assessment)? We hypothesize that the risk model may identify people who miss or refuse screening, deny risk because they do not believe themselves to be at risk or feel ambivalent, or deliberately conceal their risk. We will test the hypothesis that the suicide risk model implementation will improve identification and recognition of patients at increased risk of suicide attempt compared to usual care.

The study will also collect implementation data as part of the process of evaluating the intervention in three health systems. We will collect information during the start-up period (to document current usual care for suicide prevention and local implementation decisions), during the intervention period (to collect information on adaptations, should they occur), and during the sustainment period (to capture lessons learned and whether and how the intervention endures). Data will be collected in the form of meeting minutes, observations, and field reports from clinical leads and champions. Additionally, surveys of clinicians who will work with the suicide risk model intervention will be conducted prior to implementation and six months following implementation.

### Study settings

The study will be implemented in behavioral health clinics in three health care systems with a long history of collaborative work; all three systems were part of the original MHRN work to develop and validate the suicide risk models [17].

### Kaiser Permanente Northwest (KPNW)

KPNW includes 10 behavioral health clinics serving approximately 50,000 patients annually, a behavioral health inpatient hospital, and a dedicated ZS implementation team. In 2007, KPNW began screening all patients attending outpatient behavioral health office visits using the PHQ9. Strategies expanded to include the C-SSRS in 2012, an EHR version of the C-SSRS in 2016 and a revision in 2018 making the data more accessible for research and quality improvement. Safety planning, means counseling, caring contacts, and cognitive behavioral therapy (CBT) are standard care.

### Henry Ford Health (HFH)

HFH has four outpatient behavioral health clinics serving > 60,000 patients annually and four behavioral health inpatient hospitals. The department has a suicide prevention task force, which oversees implementation, evaluation, and quality improvement for the ZS Program, which have been implemented since 2001. Indeed, ZS was developed from the Perfect Depression Care [27–29] initiative at Henry Ford; this site has a long history of international leadership in suicide prevention. In 2018, HFH updated its ZS protocols, including use of universal screening along with suicide risk assessment, safety planning, caring contacts, care coordination, and a comprehensive means safety protocol. All psychotherapists are trained in CBT. The health system also implemented a dialectical behavioral therapy program for suicide prevention.

### HealthPartners (HP)

HP is an integrated health care system with 39 behavioral health clinics serving approximately 58,000 patients annually. HP has used the PHQ9 since 2007. More recently, HP behavioral health and primary care leadership has been active in a statewide collaborative to implement ZS led by the Institute for Clinical Systems Improvement. This has included a roll-out of a depression express lane in HP’s EHR, including integration of the C-SSRS and safety planning. The MHRN suicide risk model was incorporated into HP’s health plan’s care management workflow in 2019 and into a pilot study of a clinical decision support tool for patients with opioid use disorder in eight primary care clinics in 2021 [30], but it has not previously been more widely implemented into behavioral health clinical care.

The three sites provide important variability in size, organizational structure, and degree of ZS implementation that will enrich outcome and covariate comparisons in the study.

### Overview of study design

The current study will use a hybrid type I effectiveness-implementation approach to test implementation of an EHR-derived suicide risk model to facilitate identification, recognition, and engagement in supportive suicide prevention services among individuals who are estimated to be at risk for suicide and receiving services in behavioral health clinics at the participating health systems. This includes a stepped wedge cluster randomized trial design [31, 32] with randomization of behavioral health clinics into three waves across the three participating health systems. This design offers a novel approach to studying service delivery interventions as it provides a baseline period without implementation followed by random and sequential crossover of clinics from usual care control to intervention until all participating clinics are exposed. All clinics will have a pre-implementation phase (baseline period). Within that, just prior to implementation, health systems will train clinicians. Clinician training materials will be provided but sites will operationalize the training according to local customs and resources. Differences in training rigor provide additional variability as they may partially account for acceptability or feasibility. Implementation begins when each randomized clinic (stratified by site) transitions from usual care to running the risk model so clinicians can observe the risk indicator (the intervention is the enhanced care model with the suicide risk model and associated clinician notification). Analyses will examine within and between clinic variation in outcomes and account for time since implementation. This design allows implementation of the intervention at all clinics during the study period, a requirement of our clinical stakeholders; similar designs have been used in other suicide prevention trials [33, 34].

Given the novelty of this intervention, it is premature to propose testing implementation strategies as it is unclear which combination of strategies would best address local determinants and support implementation and effectiveness. Instead, we will leverage findings from our preliminary studies [35–38] in an implementation tool kit to help our clinical partners customize implementation plans for their local context. We will describe and measure use of the tool kit and implementation determinants, strategies, and outcomes hypothesized to impact the effectiveness of the intervention to prepare for future implementation work if the model proves successful. The tool kit will be revised based on adopter and clinician feedback.

### Clinic randomization and eligibility

Sites will provide a list of behavioral health clinics to the lead analytical site (HFH). The goal is to randomize clinics into two or three waves each starting approximately three to six months apart with all waves eventually participating in the intervention (see Fig. 1). Randomization across sites will be conducted in SAS 9.4 with a simple randomization procedure (PROC SURVEYSELECT), to determine which clinics will enter the implementation period first.

**Fig. 1 Fig1:**
[figure not shown]
Stepped wedge design and study timeline

All individuals being seen in behavioral health care in one of the participating clinics are eligible for the trial, there are no exclusion criteria. Individuals included in the trial are not prohibited from seeking any care or services. Enrollment is anticipated to end July 2025.

### Implementation conceptual framework

We will use the Exploration, Preparation, Implementation, and Sustainment (EPIS) framework [39] to guide implementation planning, execution, and evaluation. This framework acknowledges that context influences implementation differently during different implementation phases and over time. This framework will help us focus on what is important as we move from planning to implementation to the process evaluation. Prior to the current study, we began the *Exploration* phase with our preliminary work [37, 38] focused on understanding determinants (within CFIR [40] categories) likely to influence suicide risk model implementation. *Preparation* will continue in year 1 among the implementation teams. Many preparations including ascertaining leadership support and identifying clinical champions, familiarizing leadership with preliminary findings related to patient and clinician preferences and recommendations for implementation, and anticipating technological and logistical requirements to enable the risk model in the EHR were already in process at the study sites prior to the study’s start. In year 1, each site will be encouraged to develop an Implementation Research Logic Model (IRLM) [41] and detailed implementation plan (see example in Fig. 2, with EPIS stages overlaid) with identified clinic champions. The IRLMs will specify known implementation determinants at each site, strategies to address the determinants, and the implementation, service, and clinical outcomes. For completeness, Fig. 2 (for illustration purposes only) also includes putative mechanisms through which the strategies may achieve the effectiveness and implementation outcomes.

**Fig. 2 Fig2:**
[figure not shown]
Implementation research logic model

### Proposed care models (mechanisms of action)

Figure 3 shows a standard suicide prevention care model (usual care) and the proposed enhanced care suicide risk model (intervention). A typical workflow that involves suicide risk identification, when a patient presents for a behavioral health visit, may begin with suicide risk screening (typically the PHQ9 [42] in the participating sites). If the PHQ9 is missed, refused, or if item 9 (“Over the last two weeks, how often have you been bothered by thoughts that you would be better off dead or of hurting yourself in some way?”) is denied, the workflow may terminate, however a clinician could also proceed if clinically indicated. Potentially terminal processes are indicated by a dark background in Fig. 3, text boxes with white backgrounds indicate continuation of the workflow. The expectation is that when patients respond positively to item 9 (i.e., respond with a score of 2 “more than half the days” or 3 “nearly every day”), a comprehensive suicide risk assessment is conducted (typically the Columbia Suicide Severity Rating Scale [C-SSRS] [43] in the participating sites). Again, if the risk assessment is missed, refused, or if risk is denied the workflow may terminate. The expectation is that when risk is confirmed, depending on acuity, a referral is made to outpatient supportive services or to the emergency department or inpatient setting.

The enhanced care suicide risk model (intervention) demonstrates the proposed changes in workflow with the risk model implementation. In this model, the suicide risk model flags the clinician in the EHR to conduct additional suicide risk screening. The expectation is that if the PHQ9 were missed, refused, or if item 9 was denied in the presence of a model-generated risk flag indicating elevated estimated risk, then the clinician would proceed to the C-SSRS as if the screening were positive.

It is important to note that among patients who present for behavioral health services, some will have minimal or no suicide risk, some will be thought to be at *clinical* risk (i.e., the treating clinician estimates the patient is at risk) [44] but will not be flagged at *estimated statistical* risk by the risk model, some will be flagged at estimated statistical risk but will deny acute clinical risk (e.g., some may have enduring suicide ideation that is being treated), and some flagged at estimated statistical risk will be confirmed, upon assessment, to be at acute clinical risk (for some this will be an incident recognition, others will already be identified and perhaps treated). The goal of the model is to prompt risk assessment of anyone determined to be at estimated elevated statistical risk, and to prompt supportive preventive services when appropriate. How care proceeds after the risk assessment is dependent on the outcome of the risk assessment and the clinician’s judgement. This is an important detail because clinicians and patients have expressed concern about risk models having the potential to lead to coercive or inappropriate treatment; the risk model prompts identification and recognition of risk but is agnostic to treatment decisions thereafter.

**Fig. 3 Fig3:**
[figure not shown]
Comparison of care models

### Data sources

Primary and secondary outcomes will be derived from EHR and administrative claims data. As members of the MHRN, all participating health systems have complete capture of EHR and claims data for their patients [14]. Additionally, all MHRN sites have structured their electronic health records and insurance claims data into locally maintained federated data systems known as the Virtual Data Warehouse (VDW) [45] at each site to support comprehensive and efficient capture of health care encounters, diagnoses, medications, patient-reported outcomes, demographics and other administrative and clinical data. We will leverage these data sources and previously validated MHRN definitions [46] for measurement of our variables. Implementation outcomes will be derived from meeting minutes, observations, field reports, and survey data collected from clinicians in participating clinics.

### Study measures and effectiveness outcomes

The primary outcome measure is fatal or non-fatal suicide attempt (binary yes/no) within 90 or 180 days of a behavioral health visit as measured using diagnosis codes for intentional self-harm (International Statistical Classification of Diseases and Related Health Problems, Tenth Revision [ICD-10] codes X60-X84; Y87.0). Suicide deaths will be ascertained from government mortality records. The denominator will be the total number of visits to behavioral health clinics and the numerator will be reported as the number of suicide attempts per 1000 visits. In addition to the primary outcome, we will examine proximal outcomes and crisis utilization measures. Proximal outcomes include measures of engagement with services documented in the EHR within the observation period. These are defined as: evidence-based suicide prevention interventions (safety planning, lethal means counseling, or caring contacts) on or after the risk identification (index) encounter, an outpatient encounter (includes telephone, virtual, and office visits) by a behavioral health clinician or psychiatrist subsequent to the index encounter, any contact with behavioral health within seven or 14 days of the index visit (includes phone calls, letters, patient portal messages, or other caring contacts in addition to encounters described above), frequency of contacts, latency to next encounter after index, and persistence in psychotherapy defined as no gap in psychotherapy visits > 90 days during the observation period. Crisis utilization measures include any encounters in the emergency department or inpatient stays subsequent to the index encounter within 90 days and 180 days.

Secondary outcomes include suicide risk identification and recognition. Identification will be measured by the number and proportion of patients estimated to be at elevated risk by PHQ9 item 9, the risk model, or both, stratified by race/ethnicity. This will be assessed at each visit, as multiple visits may occur for the same individual. However, when calculating identification and recognition, we will aggregate visits at the individual level—categorizing outcomes as yes/no for binary measures and recording the number of identifications and recognitions as count outcomes. Aggregated assessment results will be generated at 90 and 180 days. Therefore, the denominator is the number of unique patients with an encounter in the study period. In the intervention clinics we will also measure the number of patients flagged by the risk model who, at the index encounter, did not complete the PHQ9 or denied item 9. Those identified by the risk flag but not through traditional PHQ-9 will represent the gain from using a model-based identification approach; in the usual care model these patients would not be identified as having elevated estimated increased risk. Suicide risk recognition will be measured by the number and proportion of patients who complete a risk assessment (C-SSRS), stratified by race/ethnicity, where the denominator is the number of unique patients with an encounter in the study period. We will also measure the proportion who completed a C-SSRS but did not have an elevated PHQ9 item 9 score but were estimated to be at elevated risk by the suicide risk model (for comparison, this will also be measured among usual care control participants as some patients will receive risk assessments independent of prompting by PHQ9 item 9 score).

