Finally, we will separately examine the impact of health care engagement and exposure to ZS evidence-based interventions as mediators of suicide attempt and use of crisis services. We will estimate direct and indirect effects in our longitudinal settings using our previously proposed GLMMs [51]. Specifically, we will test the effect of the intervention (risk model study group, yes/no) on behavioral health service engagement (yes/no within 7 and 14 days via path ‘*a’*) and the effect of behavioral health service engagement on suicide attempt outcome (yes/no within 90 and 180 days via path ‘*b*’). The residual effect of the intervention unaccounted for by behavioral health service engagement will be tested via path ‘*c*’. We will also test a separate path model of exposure to documented suicide prevention interventions and their impact on suicide attempt outcomes using the same modeling approach. These models will include both individual documented supportive outpatient interventions for suicide and multiple interventions bundled together; we will also repeat these analyses for crisis services outcomes.

We will address missing data using multiple imputation or inverse probability weighting, depending on the nature and extent of missingness. Additionally, if the proportion of missing data is substantial, we will conduct sensitivity analyses to assess its potential impact on our findings.

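### In the mediation models for crisis services, an emergency visit or admission arising from the index visit is already the outcome and also limits the mediator, so early engagement can look protective when it has no effect.

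*Protocol article*

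**What the plan says.** Four statements in the protocol article bear on this.

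- **Mediator.** Under Study measures and effectiveness outcomes, early engagement is "any contact with behavioral health within seven or 14 days of the index visit". The contact list "includes phone calls, letters, patient portal messages, or other caring contacts in addition to encounters described above"; the encounters named just before it are outpatient ones (telephone, virtual and office).
- **Outcome.** The same section defines crisis utilization as "any encounters in the emergency department or inpatient stays subsequent to the index encounter within 90 days and 180 days".
- **Where the index visit can lead.** Under Proposed care models (mechanisms of action), once risk is confirmed, "depending on acuity, a referral is made to outpatient supportive services or to the emergency department or inpatient setting".
- **Model.** Under Analysis plan for effectiveness outcomes, engagement and exposure to suicide prevention interventions are both to be examined as mediators of suicide attempt and of crisis service use. Path a runs from intervention to 7- and 14-day engagement, and path b from engagement to the outcome. After describing this for suicide attempt, the article adds "we will also repeat these analyses for crisis services outcomes".

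The article gives no separate rule for patients who go to acute care directly from the index visit.

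**The concern.** A mediation model needs the mediator to come before the outcome. Here both clocks start at the index visit. For a patient sent from that visit to the emergency department or an inpatient unit, the outcome has happened at or near time zero, before any follow-up contact could take place. The same event then takes up some or all of the 7 or 14 days in which outpatient contacts are counted. One event therefore fixes the outcome and pushes the mediator towards no.

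This does not require the intervention to change the number of admissions. The link between low engagement and crisis use appears within each exposure period, so path b is distorted even if the share admitted is identical before and after implementation. The covariates named for the models (such as age, sex, race/ethnicity, calendar month and visit frequency) do not include disposition from the index visit, so they would not remove it.

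At stake is the mechanism claim for crisis services: that prompt follow-up after the index visit lowers later emergency and inpatient use. The indirect effect is built from paths a and b and would inherit the error in path b.

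**Working it through.** The article states no admission share, contact rate or crisis rate, so there is no published figure to reproduce. What follows is a sensitivity calculation, and every input is an assumption.

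**Inputs**
- a = share of index patients who go to acute care directly from the index visit: 2%, 5% or 10%
- contact within the window among everyone else: 60%
- crisis risk among everyone else: 10%, the same with or without contact, so the true effect of engagement is nil
- crisis outcome in those admitted at index: 100%, by definition
- c = contact in those admitted at index: 0% at first, then relaxed

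**With c = 0**

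Odds of crisis use in engaged patients: 0.10/0.90 = 0.1111.

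Odds in non-engaged patients: [(1−a) × 0.4 × 0.10 + a] / [(1−a) × 0.4 × 0.90].

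| a | Non-engaged odds | OR, engaged vs not |
|---|---|---|
| 2% | (0.0392 + 0.02)/0.3528 = 0.1678 | 0.66 |
| 5% | (0.038 + 0.05)/0.342 = 0.2573 | 0.43 |
| 10% | (0.036 + 0.10)/0.324 = 0.4198 | 0.26 |

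The true OR is 1.00 in every row.

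**Relaxing the no-contact assumption**

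Some admitted patients will be discharged and contacted inside the window, or be sent a letter or message. The engaged odds become [(1−a) × 0.06 + a × c] / [(1−a) × 0.54], and the non-engaged odds [(1−a) × 0.04 + a × (1−c)] / [(1−a) × 0.36].

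- c = 30%, a = 2%: (0.0648/0.5292) / (0.0532/0.3528) = 0.81
- c = 30%, a = 5%: (0.072/0.513) / (0.073/0.342) = 0.66
- c = 60%, the same as everyone else: OR = 1.00 at any a

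The distortion comes from the lower opportunity for contact, and it vanishes if admitted patients are contacted as often as others.

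**After the fix**

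With c = 0, leave the index event out of the outcome and let admitted patients have a later crisis risk r. The non-engaged odds are [(1−a) × 0.04 + a × r] / [(1−a) × 0.36 + a × (1−r)].

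- r = 10%, as in others: OR = 1.00 at any a
- r = 20%, a = 2%: 0.1111 / (0.0432/0.3688) = 0.95
- r = 20%, a = 5%: 0.1111 / (0.048/0.382) = 0.88

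The built-in part goes. What remains is ordinary confounding, if admitted patients are sicker.

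**The case against.** **It may be a coding detail for the analysis plan.** The article is condensed, refers to previously validated definitions, and may be backed by a plan that handles admitted patients. That is fair for the date rule itself. But the article does fix the time zero, the window, the contact list, the mediator and the crisis outcome, and running the crisis-services mediation from those definitions as stated produces the problem. One could read the word subsequent in the crisis definition as leaving out care arising from the index visit, but nothing in the article says so.

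**The inputs are invented.** This stands. The odds ratios show direction and sensitivity and do not forecast this trial. If the index population were all visits rather than risk-identified ones, the admitted share, and with it the bias, would be smaller.

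**Remedies that use admission status bring their own bias.** This also stands. Admission follows exposure and may be affected by it. Restarting the clock at discharge gives admitted patients a different time zero, and restricting to patients not in hospital conditions on a post-exposure event. Neither should be the main analysis.

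**A stronger reading is tempting.** A reader might infer that the direction of the engagement result itself depends on admissions, down if a stay does not count as contact and up if it does. The documents do not support this. The contact list is outpatient and inpatient stays sit under crisis use, so counting a stay as engagement is a weak reading. With equal admission shares the sign does not change: 50% versus 52% true engagement with 2% admitted in both periods gives 0.98 × 2 = 1.96 points. With admitted patients scored as not engaged and 2% admitted in the control period, reversal needs an intervention-period share above 1 − 0.98 × 0.50/0.52 = 5.8% for a true gain of 2 points. The thresholds are 10.9% for 5 points (0.55 in the denominator) and 18.3% for 10 points (0.60). Nothing in the article points to such differences.

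**Conclusion.** The concern holds for the mediation models repeated for crisis services, and only there. As defined, the outcome can come before the mediator and restrict it, which biases path b towards an apparent protective effect of engagement even when admission shares are equal across periods. Under no true effect, the illustrative odds ratio is 0.66 at a 2% index-admission share and 0.43 at 5% if admitted patients have no contact in the window, and 0.81 and 0.66 if 30% of them do. The actual size is unknown, because the article gives neither the share admitted at index nor the contact and crisis rates.

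The models for suicide attempt do not share this fault, since an admission is not itself that outcome. The primary outcome is unaffected. This is a minor but real defect in an explanatory analysis.

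**What to change.** 1. In the crisis-services mediation models, do not count emergency visits or admissions that begin from the index visit as the outcome. Keep them in the separate total-effect analysis of crisis use, so that acute care the intervention itself prompts is still reported.
2. State that an inpatient stay is not itself engagement in the 7- and 14-day measure.
3. Report the share admitted from the index visit by exposure period, so that readers can judge how far it matters.
4. Run a clock starting at discharge, and a restriction to patients not in hospital during the engagement window, as sensitivity analyses only.

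The cost is a few sentences in the analysis plan and a date rule using encounter data already needed for the crisis outcome. The downside is that the mediation outcome no longer covers crisis use arising directly from the index visit, and some confounding by severity may remain. The change concerns measurement and analysis only and does not touch care.
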